## 1.0 Objectives

1. Determine whether the vascular phenotype (average vessel length, number of open lumens, number of endothelial cell sprouts, pericyte coverage of vessels) of pancreatic adenocarcinoma is associated with patient pre-surgery physical activity level.
2. Determine whether the number of infiltrating immune cells in pancreatic adenocarcinoma is associated with pre-surgery physical activity level.
3. Determine whether serum levels of angiogenic factors are associated with patient physical activity level.

## 2.0 Rationale

Chemotherapy and/or radiation therapy is administered to patients with potentially curable pancreatic adenocarcinoma (PDAC) prior to pancreatectomy (1, 2). Chemotherapy efficacy is dependent on chemotherapy access to the tumor cells, via tumor vasculature. However, PDAC tumors are poorly perfused with compressed, dysfunctional tumor vasculature that ineffectively delivers chemotherapy to the tumor (3).

In mouse models of PDAC, we demonstrated that moderate aerobic exercise changed the tumor vascular phenotype. Tumors from exercised mice had longer vessels with more open lumens, and a 24% increase in the percentage of functional blood vessels (fig 1). Importantly, the combination of exercise and gemcitabine correlated with better delivery of chemotherapy to PDAC tumors and with significantly better inhibition of tumor growth than gemcitabine alone (fig 2). In our mouse models, we identified Thrombospondin-1 and Sphingosine-1-Phosphate as circulating angiogenic factors that are responsible for improved tumor vascular function due to exercise. Further, preclinical evidence suggests that exercise may increase the number of cytotoxic NK cells recruited a tumor, further bolstering anti-tumor effect (4). If our findings in mice accurately represent human tumors, this would be compelling evidence to support exercise as an adjuvant to chemotherapy. We therefore propose a retrospective lab study to evaluate vascular phenotype and immune cell infiltration in PDAC samples, and to correlate these findings with patient physical activity levels.

[figure not shown]

[figure not shown]

**Fig 2. Gemcitabine is more effective when combined with exercise.** PDAC-tumor bearing mice were treated with 15mg/kg gemcitabine 3x weekly, and performed moderate treadmill running 5 days/week for 2 weeks or were in the control group. Tumor volume over time is shown, n=5 per group, \*p<0.05.

### 3.0 Eligibility of Subjects

1. Patient is enrolled on 2014-0702.
2. Patient has agreed to banking of samples and use of samples in future research, and has samples available for analysis through Protocol PA11-0670.

### 4.0 Research Plan and Methods

**Tissue Source:** For PDAC tumor tissue, sections from surgical specimens collected under protocol Lab00-396 (PSC), or from the MD Anderson tissue bank will be used. For serum samples, blood collected under PA11-0670 will be used.

**Tissue Sample Number:** Samples will be divided into “control, unknown physical activity” or “documented preoperative physical activity” groups. For control, unknown physical activity group, 30 tumor samples and 30 blood samples will be evaluated. Samples will be classified as “documented preoperative physical activity” if the samples were obtained from patients who participated in the Preoperative Rehabilitation during neoadjuvant therapy for pancreatic cancer (2014-0702) study and therefore detailed documentation of the patients’ physical activity can be obtained. For this group, 60 tumor samples and 60 blood samples will be evaluated.

**Immunohistochemistry:** Standard immunohistochemistry staining protocols will be used to stain tumor sections for CD31 or CD34 (endothelial cells), α-Smooth Muscle Actin (pericytes/smooth muscle cells), CD8, CD4 (T cells), or CD94 (NK cells). After staining, 5 random 10x magnification fields per tumor will be photographed, and the following will be quantified and averaged to obtain one value per patient: microvessel density, number of blood vessels per field, average vessel length, number of open lumens, number of endothelial cell sprouts, number of CD8+ cells, number of CD4+ cells, number of CD94+ NK cells.

**Serum Thrombospondin-1 and Sphingosine-1-Phosphate:** Serum will be collected and batch processed, 10 samples at a time. Commercially available ELISAs for human Thrombospondin-1 and Sphingosine-1-Phosphate.

Association with Patient Characteristics: Patient medical records will be used to classify each patient as either: Unknown Physical Activity, 0-60 minutes weekly Physical Activity, 60-120 minutes weekly Physical Activity, or >120 minutes weekly Physical Activity. Values for all measured variables will then be grouped by physical activity levels and compared for associations.

## 5.0 Statistics and Justification of Sample Size

---

The major objective of this study is to correlate pre-surgery activity level with vascular phenotype and infiltrating immune cells (i.e. CD8+, CD4+ and CD94+ NK cells) in pancreatic adenocarcinoma, as well as to correlate pre-surgery activity level with serum level of angiogenic factors Thrombospondin-1 and Sphingosine-1-Phosphate. Vascular phenotype outcomes include microvessel density, number of blood vessels per field, average vessel length, number of open lumens.

Tumor and blood sample from two groups of patients, i.e. control, unknown physical activity or documented preoperative physical activity, will be studied. 30 tumor samples and 30 blood samples will be evaluated for patients with unknown pre-surgery physical activity, while 60 tumor samples and 60 blood samples will be evaluated for patients with documented preoperative physical activity, and patients in this group will be classified based on their duration of weekly physical activity as three groups: 0-60 minutes, 60-120 minutes and > 120 minutes, with an expected proportions of 25%, 50% and 25% for each group, respectively. We will use ANOVA with pairwise comparisons to compare vascular phenotype outcomes, number of infiltrating immune cells and angiogenic factors between groups with different activity levels, and will adjust for multiple tests using Tukey's method. Or we will use non-parametric alternatives Kruskal-Wallis test or Wilcoxon rank sum test if the assumption of normality is not satisfied. Sample size justification was calculated based on comparison of one outcome between any two groups with different activity levels, using a two-sided two sample t test at a significance level of 0.008 (Bonferroni method adjusted). A sample size of 15 samples per group will have 80% power to detect an effect size (i.e. the expected difference in means divided by the common standard deviation) of 1.362 in the measured outcome between two comparison groups. A sample size of 30 samples in one group and 15 in the other group will have 80% power to detect an effect size of 1.152. While a sample size of 30 samples per group will have 80% power to detect an effect size of 0.93. With sample size increases, 80% power will be able to detect a smaller effect size. In addition, we will also fit multivariate linear regression models to compare vascular phenotype outcomes, infiltrating immune cells and angiogenic factors among patient group with different levels of physical activity, adjusting for the effects of patient baseline characteristics. In the event that the normality assumption is not satisfied, data transformation will be performed.

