We aim to recruit roughly equal numbers of male and female participants and participants who met/exceeded or did not meet baseline recommendations for walking and resistance exercise. However, we recognize that differences in interest and availability can affect recruitment, and we may have imbalances in these proportions. Recent qualitative research studies examining influences and outcomes related to physical activity among cancer survivors have reached saturation of themes after interviewing five [12] and nine [13] participants. Ten of the 20 patients enrolled in the original 2014-0702 prehabilitation protocol underwent surgery, and we expect approximately 50% of the 50 patients who have enrolled or will enroll in the current (revised) protocol to undergo surgery. Therefore, we will have access to approximately 35 patients who are possible candidates for this study. We expect to conduct approximately 12-15 interviews among this group. Qualitative analysis of interview transcripts will occur on a rolling bases, however, and we will end recruitment and cease interviewing upon reaching saturation of qualitative themes.

The following is a list of interview topics and questions:

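### The 60 tumor samples planned for the documented-activity group conflict with the protocol's own forecast of about 35 resected patients, and at 35 the stated detectable effects are not reached for the tumor outcomes

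*Protocol*

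**What the plan says.** **Tissue study (sections 4.0 and 5.0).** The control group is small and fixed: "30 tumor samples and 30 blood samples will be evaluated for patients with unknown pre-surgery physical activity". For the other group the plan is "while 60 tumor samples and 60 blood samples will be evaluated for patients with documented preoperative physical activity". Section 4.0 places a sample in that group "if the samples were obtained from patients who participated in the Preoperative Rehabilitation during neoadjuvant therapy for pancreatic cancer (2014-0702) study". It takes tumor sections from surgical specimens or from the institution's tissue bank, and averages five fields so that each patient contributes one value. Section 5.0 divides the documented group into low (0-60 minutes a week), middle (60-120) and high (over 120), "with an expected proportions of 25%, 50% and 25% for each group, respectively", which is 15, 30 and 15 of 60.

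The power statement uses a two-sided two-sample t test at 0.008. It begins "A sample size of 15 samples per group will have 80% power to detect an effect size" of 1.362, and goes on to 1.152 for 30 against 15 and 0.93 for 30 against 30.

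**Accompanying protocol 2014-0702 (section VII).** Twenty patients were enrolled under the first design and 50 more are planned. The Study Measures part reports that 10 of the first 20 had surgery and adds that "we expect approximately 50% of the 50 patients who have enrolled or will enroll in the current (revised) protocol to undergo surgery". It then totals these: "Therefore, we will have access to approximately 35 patients who are possible candidates for this study". Earlier in section VII, the sample-size paragraph splits the 50 new patients into three pathways of 35, 10 and 5, each ending in surgery.

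**The concern.** Sixty values at one per patient need 60 participants of 2014-0702 with tumor tissue. The only explicit forecast of how many will be operated on is about 35. If that is right, the groups of 15, 30 and 15 behind the power statement will not be filled for the vascular and immune-cell outcomes (objectives 1 and 2).

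The sample-size section is the only place where a reader learns how large an association the study could detect. If the tumor groups are little more than half the planned size, those figures are too favourable. A non-significant tumor result could then be given more weight than it can bear. The comparison between the least and most active patients, the widest exercise contrast in the study, loses most.

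**Working it through.** **1. Reproduce the plan's figures.** For groups of n1 and n2 and a standardised difference d, power is the probability that a noncentral t variable with n1 + n2 − 2 degrees of freedom and noncentrality d / √(1/n1 + 1/n2) exceeds the two-sided critical value at 0.008 (the opposite tail is negligible). Four groups give six pairwise comparisons, and 0.05/6 rounds to 0.008. Solving for 80% power:

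| Groups | Stated | Recomputed |
|---|---|---|
| 15 v 15 | 1.362 | 1.3621 |
| 30 v 15 | 1.152 | 1.1523 |
| 30 v 30 | 0.93 | 0.9304 |

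The stated effects are correct for the stated group sizes.

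**2. Count the tumors.**
- Enrolled on 2014-0702: 20 + 50 = 70.
- Study Measures forecast: 10 + 0.5 × 50 = 35, which is 25 short of 60, or 58% of plan.
- Pathway assumption in section VII: 35 + 10 + 5 = 50 new patients, all reaching surgery; 50 + 10 = 60.
- Resection rate needed for 60: 60/70 = 86% overall, or all 50 of the new patients, against 50% observed and forecast.

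**3. Recompute at about 35 tumors.** The 25/50/25 split gives 8.75/17.5/8.75, taken as 9/17/9, with 30 controls, alpha 0.008 and 80% power.

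| Contrast | n | Stated effect | Effect at 80% power | Power at stated effect |
|---|---|---|---|---|
| Low v high | 9 v 9 | 1.362 | 1.85 | 47% |
| Low or high v middle | 9 v 17 | 1.152 | 1.56 | 48% |
| Low or high v control | 9 v 30 | 1.152 | 1.40 | 59% |
| Middle v control | 17 v 30 | 0.93 | 1.10 | 62% |

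As an example of the last column, for 9 v 9 the noncentrality is 1.362 / √(1/9 + 1/9) = 2.889 and the critical value on 16 degrees of freedom is 3.028, so power is 47%. Using the fractional sizes instead gives 1.89, 1.56, 1.41 and 1.09, with power of 45%, 47%, 58% and 63%.

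**4. Range.** The exact 95% interval for 10 of 20 is 27% to 73%. Assuming the new cohort's rate lies in that range, total resections run from 10 + 50 × 0.272 = 23.6 to 10 + 50 × 0.728 = 46.4, about 24 to 46. Effects are in the order of the table above.
- At 46 (11.5/23/11.5): about 1.59, 1.33, 1.27 and 1.00; power at the stated effects is 63% to 72%.
- At 24 (6/12/6): about 2.46, 1.97, 1.65 and 1.25.

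The stated effects are not reached with 80% power anywhere in this range.

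**5. Serum.** Section 4.0 takes blood from PA11-0670 and does not make resection a condition. Seventy enrolled patients could supply 60 samples if about 86% have banked blood. The documents give no rate.

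**The case against.** **The protocol also supports 60.** The pathways in section VII send all 50 new patients to surgery, and adding the 10 earlier resections gives exactly the tissue target. This stands, and it means that the documents conflict with each other; they do not uniformly say 35. But the pathways set the denominators for adherence by treatment phase. The Study Measures text is an explicit forecast based on what happened in the first cohort, and the same text provides for participants who are not resected.

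**The 35 is approximate and was made for another purpose.** It shows that 12 to 15 interviews can be found, and it was written during accrual. That is fair, and it is why a range is needed. The range still falls short of 60.

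**Tissue-bank material is also allowed.** The documents do not say whether the bank holds usable tumor from unresected participants. The documented group would still have to be 2014-0702 participants. That study admits suspected as well as biopsy-proven disease, and a diagnostic biopsy taken before the program would predate the exercise under study. Bank tissue cannot be ruled out, so its absence is stated here as an assumption.

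**The power statements are conditional and true.** They are, and a reader who inferred a calculation error would be wrong. What is in doubt is the number of tumors to which they apply.

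**Conclusion.** The point holds as an unreconciled conflict over the number of tumors, with a material effect on the sample-size justification for objectives 1 and 2. On the protocol's explicit forecast, the detectable effects rise by about 0.17 to 0.49 standard deviations, and power at the stated effects is about 47% to 62% instead of 80%. This rests on three assumptions: about 35 resections, no usable tumor from unresected participants, and the stated 25/50/25 split.

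Three stronger readings are not supported:
- **That 60 tumors are impossible.** One part of section VII implies 60, so the documents support only that 60 is not expected on the explicit forecast.
- **That the tumor study has under 50% power throughout.** This is true of the two contrasts among activity groups (47% and 48%), but not of the contrasts with control (59% and 62%).
- **That the serum objective fails too.** Nothing in the documents ties the blood samples to resection.

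**What to change.** - Reconcile sections 4.0 and 5.0 with the two parts of section VII, and state one expected number of resected 2014-0702 participants with its basis.
- In 4.0 and 5.0, justify the tumor and serum numbers separately.
- For tumor outcomes, give the detectable effects at about 35 samples (about 1.85, 1.56, 1.40 and 1.10 on the 9/17/9 split with 30 controls), with a range such as 24 to 46. Naming 35 as a new fixed target would repeat the problem, because the banking condition in section 3.0 can only lower the count.
- State whether the tissue bank can supply tumor from unresected participants.
- Keep 60 for serum only if banked blood from unresected participants supports it.

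The cost is a wording amendment and less favourable stated detectable effects for the tumor outcomes. No extra patients are needed.

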#### ***Nutrition intervention***

Within 7 days of enrollment, a registered dietitian (RD, ie the study dietitian or delegate RD) will conduct a complete nutritional assessment. Each subject will be then be provided with individualized recommendations for calorie, protein, and fluid intake, tools for tracking intake (ie, diet log), as well as goals for weight maintenance, weight gain, or weight loss depending on stage of treatment/recovery. Patients will also be instructed to eat a high protein snack/meal/shake (~20 g) within one hour after strengthening exercises.

As is current “standard of care” for our patients who undergo pancreatic surgery, all patients will also receive instruction on the use of an immune enhancing oral supplement (Impact Advanced Recovery) for 5 days preoperatively (preop days 6 through 1).

When the research staff contacts the participants via telephone to monitor their exercise program, they will also be asked questions regarding their compliance with the nutritional plan. The research staff will be provided with a list of questions to assess patient understanding of and ability to comply with nutrition recommendations. If patients are non-compliant or have difficulty comprehending the nutritional program, the RD will be notified and RD will follow up with the patient for reeducation or adjustment of goals. To monitor compliance with immune enhancing oral supplement, the patient/family will be interviewed following surgery to determine consumption.

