## **VII. Statistics**

This is a pilot study to assess the feasibility of a provider-supervised prehabilitation program among pancreatic patients who are undergoing neoadjuvant therapy. The prehabilitation program will include both exercise and nutrition interventions, where the exercise intervention will incorporate resistance/strengthening and walking programs. Adherence will be defined as the ability of each patient to complete  $\geq 60\%$  of the planned exercise intervention based on the total time spent performing the exercises relative to the total duration of therapy or total duration of recovery for a given phase. The primary endpoint, feasibility, will be established if  $\geq 60\%$  of the patients are adherent during a phase of therapy. That is, the prehabilitation program is deemed as feasible during a specific phase of therapy if 60% or more of the participants complete at least 60% of the weekly prescriptions for 60 minutes of walking and 60 minutes of strengthening

exercises during that phase of therapy. The calculation will account for the potential difference in the length of therapy among patients. The target weekly total exercise hour will be 120 minutes (including 60 minutes of walking and 60 minutes of strengthening exercises), thus we can derive the total prescribed hour for a given patient in a given phase considering his/her total treatment or recovery duration for that phase. Then, based on the recorded total hours of exercise intervention for that patient, we can calculate the % of completion for that patient in a given phase. If the % is at least 60% for a phase, we would define that patient as “adherent” for that phase. For the primary analysis, we will analyze the % adherence by phase, where “phase” could be chemotherapy phase, chemoradiation phase or recovery phase. As a secondary analysis, we will further differentiate whether patients receive chemoradiation from start or chemoradiation is given following chemotherapy and analyze these two subgroups of patients separately. Similarly, we will differentiate patients in recovery phase based on the therapies they receive prior to the recovery (i.e., chemotherapy only, chemoradiation only or chemotherapy plus chemoradiation).

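### Contrasts with the unknown-activity controls reflect an exercise-plus-nutrition programme, but section 5.0 treats them as comparisons of activity level

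*Protocol*

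**What the plan says.** The laboratory protocol (sections 1.0 to 8.0) forms its groups in section 4.0. A sample counts as documented activity "if the samples were obtained from patients who participated in the Preoperative Rehabilitation during neoadjuvant therapy for pancreatic cancer (2014-0702) study"; 60 tumor and 60 blood samples are planned. The control group, 30 and 30, is defined only by unknown activity. Section 4.0 then lists unknown activity beside the three weekly-minute bands as one of four classes to be compared.

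Section 5.0 applies ANOVA with Tukey-adjusted pairwise comparisons, or rank tests, to groups it describes as differing in activity level. It adds regression models to "compare vascular phenotype outcomes, infiltrating immune cells and angiogenic factors among patient group with different levels of physical activity", adjusting for baseline characteristics.

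The accompanying 2014-0702 protocol describes what the documented patients received. Section VII states: "The prehabilitation program will include both exercise and nutrition interventions". Under Nutrition intervention, each subject has a dietitian assessment and is "provided with individualized recommendations for calorie, protein, and fluid intake, tools for tracking intake", with dietitian follow-up if compliance is poor. One element is linked to exercise sessions: "Patients will also be instructed to eat a high protein snack/meal/shake (~20 g) within one hour after strengthening exercises". Section III makes adherence to the nutrition intervention a secondary endpoint.

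**The concern.** In any comparison of controls with documented patients, activity is not the only thing that differs. The documented side also had a structured nutrition programme, delivered after baseline, so adjustment for baseline characteristics does not address it. No added covariate can separate the two in this contrast either: as far as the document shows, having the plan and belonging to the documented group coincide, and no nutrition adherence is recorded for controls.

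Interpretation is at stake. Section 2.0 says that human results matching the mouse findings would be compelling support for exercise as an adjuvant to chemotherapy. A difference from controls in vessels, immune cells or serum factors, reported under an activity-level label, may be read that way when it could equally reflect the nutrition component.

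**Working it through.** **1. How many comparisons are affected.** Section 5.0 tests at 0.008, described as Bonferroni adjusted. Four groups give 4 × 3 / 2 = 6 pairs, and 0.05 / 6 = 0.0083, close to 0.008. The plan therefore counts controls as one of the activity groups. Three of the six pairs involve them.

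**2. Which comparisons these are.** The expected split of the 60 documented patients is 25%, 50%, 25%: 0.25 × 60 = 15, 0.50 × 60 = 30, 0.25 × 60 = 15. Controls number 30. The plan's detectable effects, checked with the exact noncentral t at two-sided 0.008, reproduce: power is 79.99% for 1.362 (15 vs 15), 79.98% for 1.152 (30 vs 15) and 79.96% for 0.93 (30 vs 30). Assigned to pairs:

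| Pair | Sizes | Detectable effect (SD) | Nutrition plan on both sides? |
|---|---|---|---|
| Unknown vs 0-60 min | 30 / 15 | 1.152 | No* |
| Unknown vs 60-120 min | 30 / 30 | 0.93 | No* |
| Unknown vs >120 min | 30 / 15 | 1.152 | No* |
| 0-60 vs 60-120 min | 15 / 30 | 1.152 | Yes |
| 60-120 vs >120 min | 30 / 15 | 1.152 | Yes |
| 0-60 vs >120 min | 15 / 15 | 1.362 | Yes |

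*If controls come from outside 2014-0702.

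The pair with the smallest detectable effect is a control contrast. The sample-size figures themselves are correct and unaffected.

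**3. Where the controls come from.** Section 4.0 defines the documented group by participation in 2014-0702, so controls should be patients outside it. Section 3.0 makes enrolment on 2014-0702 an eligibility criterion for every subject. Both cannot hold for a separate control group.

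**4. What can differ within the documented group.** The dietitian plan is given to each subject, so it is common to the three bands. Two routes remain. The protein advice follows strengthening sessions, so intended intake rises with their number; walking, half of the 120-minute weekly target (60 of 120), carries no such advice. And diet and exercise compliance are pursued on the same telephone calls, so the two may be correlated. Neither is a baseline characteristic.

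**The case against.** **The aims are only associational.** Sections 1.0 and 5.0 speak of association and correlation, and the sentence in section 2.0 is a conditional rationale. This stands against any claim that the plan will attribute differences to activity. It does not remove the problem: even an association with activity level is mislabelled when one side of the contrast has no known activity and the other had a second intervention.

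**The supplement.** A reader might infer that the immune-enhancing supplement taken shortly before resection confounds the immune-cell outcomes, especially as its use is recorded: "To monitor compliance with immune enhancing oral supplement, the patient/family will be interviewed following surgery to determine consumption". The document does not support this. The supplement is introduced with the words "As is current “standard of care” for our patients who undergo pancreatic surgery", so resected controls at the same centre would be expected to receive it too. Nothing shows that uptake differs between groups.

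**The size.** It is tempting to put a bias in SD units. The documents give neither a nutrition effect nor compliance by activity band, so any such figure would be invented.

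**Controls' nutritional care is not described.** This is fair: that they lacked the plan is inferred from silence, and section 3.0 clouds their source. The point is conditional on that.

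**The remedy belongs in an analysis plan.** This holds for the choice of sensitivity covariates. It does not hold for the control contrast, where only a change in the stated interpretation helps.

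**Over-adjustment.** Protein after a session may be part of the exercise prescription, so adjusting for it could remove some of the exposure's own effect. This stands, and it confines nutrition adherence to a sensitivity model.

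**Conclusion.** The concern holds in a limited form. Assuming controls come from outside 2014-0702 and did not receive its nutrition plan, three of the six planned pairwise comparisons, including the one with the smallest detectable effect, reflect exercise plus nutrition and not activity alone. If controls were instead 2014-0702 participants, as section 3.0 would require, this part weakens.

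Within the documented group the possible confounding is narrower: post-strengthening protein and any correlation between diet and exercise compliance. A reader might infer that the dietitian plan as a whole confounds the comparison among bands; it does not, because all three bands receive it. The magnitude is unknown in either setting.

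**What to change.** In section 5.0:

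1. State that contrasts with the unknown-activity group reflect the exercise-plus-nutrition programme and are not evidence about physical activity level. Base activity conclusions on the comparison among the three documented bands.
2. As a sensitivity analysis only, add 2014-0702 nutrition adherence to the regression within the documented group. Report whether the activity coefficient changes, and note the possible over-adjustment.

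Reconcile sections 3.0 and 4.0 on where controls come from, since item 1 depends on it.

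The cost is wording and one secondary model, with no change to treatment, sample size or specimens. Adherence is already a 2014-0702 endpoint and compliance is asked about by telephone, but the protocol defines no scored adherence variable, so one must be specified first. Intervals in that model will probably be somewhat wider. Activity conclusions would rest on pairs with detectable effects of 1.152 and 1.362, without the 0.93 pair. That pair did not compare known activity levels in the first place.
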